## Methods

### Study Design

A randomized, single-blind, parallel-controlled trial will be undertaken to assess the impact of acupuncture on enhancing cognitive function in individuals with PSCI. A total of 54 participants will be recruited and randomly allocated to either the acupuncture group or the conventional treatment control group. The intervention will span 8 weeks, with cognitive evaluations scheduled at baseline, 4 weeks after treatment, and 8 weeks after treatment. Previous trials have shown that such frequency and intensity of treatment are both safe and effective in improving cognitive outcomes in survivors of stroke [34,35]. Participant attendance will be closely monitored. Any missed sessions will be documented along with reasons, and efforts will be made for rescheduling. Treatment logs will be maintained by treating physicians to record each session, including date, time, and whether the session was completed as scheduled.

### Sample Size

The primary outcome of this study is the change in cognitive function as measured using the Beijing version of the Montreal Cognitive Assessment (MoCA). We prespecified a standardized between‑group effect size of *d*=0.40 on the MoCA at 8 weeks. This assumption is supported by a recent meta‑analysis of acupuncture for PSCI showing a pooled mean difference (MD) of 3.30 points (95% CI 2.19-4.40) versus control [36,37]. Using representative poststroke variability (MoCA score mean 21.1, SD 7.5), an MD of 3.30 corresponds to a standardized effect of approximately 0.44; thus *d*=0.40 is conservative. Therefore, the trial is powered on MoCA as the primary cognitive end point.

Using G Power (version 3.2.7) with a 2-tailed test, α set at.05 (type I error), and power (1 – β) at 0.80 (type II error β=.20), the minimum required sample size was calculated to be 44 participants (22 per group) [38]. To account for an anticipated 20% dropout or loss to follow-up rate, the total sample size was increased to 54 participants, with 27 participants allocated to each group.

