##### Sham Acupuncture Procedure

Sham acupuncture will be administered at nonacupoint sites approximately 2 cm posterior to Baihui (GV20), 1.5 cm lateral to Shenting (GV24), and 2 cm adjacent to Sishencong (EX-HN1), avoiding recognized meridians [40]. A nonpenetrating placebo needle will provide superficial tactile pressure without skin penetration, mimicking real acupuncture sensation but avoiding physiological effects [41]. Sessions will last 20 minutes once daily, 5 days per week for 8 weeks.

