**Brand New Insights**

A suite of analyses, including independent component analysis, functional connectivity analysis, and DTI analysis, will be conducted before and after the intervention to assess changes in activation patterns, functional connectivity, and structural connectivity within brain regions associated with the DMN. Correlation analyses between changes in DMN and cognitive function will be conducted to elucidate the neuroimaging correlates of the structural and functional changes within the DMN.

Crucially, all participants will receive standardized cognitive rehabilitation as part of routine clinical treatment throughout the trial, with both the acupuncture treatment group and the sham acupuncture group undergoing the same treatment regimen. This design intentionally sets cognitive training as a constant therapeutic background to isolate the specific effects of acupuncture from nonspecific placebo responses. Therefore, the observed differences between groups will solely represent the contribution of acupuncture points to neuropsychology rather than absolute treatment outcomes. This method rigorously controls cognitive training variables, precisely quantifies the incremental benefits of acupuncture based on evidence-based rehabilitation, and simulates real-world practice to demonstrate the clinical relevance of acupuncture as an adjunctive treatment. Consequently, effect sizes should be interpreted as the added value of acupuncture to a standard cognitive program, with the differences controlled via sham stimulation directly attributable to the specific neural stimulation mechanisms of acupoints.

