**Limitations and Future Directions**

While the randomized controlled trial and blinding methodologies are upheld, the feasibility of achieving total blindness has been acknowledged as challenging, particularly in nondrug trials. Given the unique nature of acupuncture treatment, a double-blind procedure is not feasible, leading to the decision to blind outcome evaluators and statistical analysts. In addition, both groups receive conventional cognitive training to ensure ethical equivalence; however, this may reduce the contrast between groups. Moreover, we acknowledge the limitations in generalizability of our study findings, primarily due to the single-center design and the constraints imposed by resource-intensive research protocols and the standardization of millimeter-level interventions. To minimize potential biases, we have implemented rigorous quality control measures. For future research, we plan to conduct multicenter trials to quantitatively assess general applicability and conduct additional real-world validation to further enhance the generalizability of our findings.

In summary, by adopting a multimodal neuroimaging approach, this study delves into the impact of acupuncture on the brain structure and function of patients with PSCI. By examining correlations with changes in cognitive function, this study aims to clarify the specific targets and mechanisms through which acupuncture enhances cognitive function. The findings are anticipated to yield reliable imaging markers for evaluating the efficacy of acupuncture and prognosis of PSCI, offering valuable clinical applications. If this study demonstrates a significant intervention effect, it will contribute robust evidence supporting acupuncture’s ability to ameliorate cognitive dysfunction in patients with PSCI, providing insights into its neuroimaging mechanisms.

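### Calling d=0.40 conservative is unsupported for a sham-controlled add-on comparison, and the stated 80% power is not delivered even at d=0.40

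*Protocol article*

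**What the plan says.** In the Protocol article, Sample Size, the effect at 8 weeks is set at d=0.40 on the MoCA. The support is a meta-analytic "pooled mean difference (MD) of 3.30 points (95% CI 2.19-4.40) versus control", standardised with a general poststroke figure ("MoCA score mean 21.1, SD 7.5") to about 0.44. Because 0.40 is below 0.44, the section calls it conservative. It then states a calculation "with a 2-tailed test", alpha "set at.05 (type I error") and power "at 0.80 (type II error β=.20"), which gives 22 per group, raised to 27 per group (54 in total) for 20% dropout.

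The comparison being randomised is described elsewhere:

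- **Cognitive Function Training:** 30 minutes daily, 5 days a week for 8 weeks. This belongs to the conventional package that both arms receive.
- **Sham Acupuncture Procedure:** "A nonpenetrating placebo needle will provide superficial tactile pressure without skin penetration, mimicking real acupuncture sensation", in 20-minute sessions, 5 days a week for 8 weeks.
- **Acupuncture Treatment Group, Overview:** the same package, with real needling replacing sham.
- **Brand New Insights:** "effect sizes should be interpreted as the added value of acupuncture to a standard cognitive program".
- **Limitations and Future Directions:** "both groups receive conventional cognitive training to ensure ethical equivalence; however, this may reduce the contrast between groups".

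The General Data and Efficacy Indicator Statistical Analysis section names a two-tailed independent-samples t test for the between-group comparison.

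**The concern.** An effect borrowed for sizing has to belong to the contrast being randomised. Here the source contrast is acupuncture against a control of unstated type, while the trial's contrast is real against sham needling with cognitive training held constant. The Discussion recognises that the contrast may be reduced, but the Sample Size section makes no visible allowance for it and describes its choice as cautious.

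Two things are at stake. A reader will take the target as having a safety margin that the stated reasoning does not supply. And a reader who trusts the 80% figure will treat a non-significant MoCA result as evidence that acupuncture adds nothing, when the trial has a low chance of detecting even its own target effect.

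**Working it through.** **Inputs, all from the Protocol article.** Source difference 3.30 points, 95% CI 2.19 to 4.40; SD 7.5; target d=0.40; two-sided alpha 0.05; power 0.80; 22 evaluable or 27 randomised per group (Sample Size). 1:1 allocation (Randomization and Allocation Concealment). Two-sample t test (General Data and Efficacy Indicator Statistical Analysis).

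**1. The standardisation reproduces.** 3.30 / 7.5 = 0.44.

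**2. The size of the allowance.**
- d=0.40 in points: 0.40 × 7.5 = 3.00.
- Allowance: 3.30 − 3.00 = 0.30 points, and 0.30 / 3.30 = 9%.
- So a loss of contrast of more than about 9% relative to the source would use up the whole margin.

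**3. The plan's own lower limit.** 2.19 / 7.5 = 0.292, which is below 0.40 before any question about the comparator arises.

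**4. The stated sample size does not reproduce.** The normal approximation is n per group = 2(1.960 + 0.842)² / d². At d=0.40 this is 2 × 7.85 / 0.16 ≈ 98.1, so 99. The noncentral t gives 99.08, so 100 per group (200 in total), against the stated 22 per group (44 in total). With 22 per group, 80% power requires d of about 0.86, or 0.86 × 7.5 ≈ 6.5 points.

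**5. Power at the planned sizes.** Noncentral t with 2n − 2 degrees of freedom and noncentrality d√(n/2):

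| n per group | d | noncentrality | power |
|---|---|---|---|
| 22 | 0.40 | 0.40 × √11 = 1.33 | 25% |
| 22 | 0.292 | 0.292 × √11 = 0.97 | 16% |
| 27 | 0.40 | 0.40 × √13.5 = 1.47 | 30% |
| 27 | 0.292 | 0.292 × √13.5 = 1.07 | 18% |

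The 27-per-group rows assume no dropout at all.

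**6. What a null result could exclude.** At SD 7.5, the 95% confidence interval for the difference has a half-width of about t × SD × √(2/n). With 22 per group this is 2.018 × 7.5 × √(2/22) = 4.6 points; with 27 it is 2.007 × 7.5 × √(2/27) = 4.1 points. Both exceed the 3.00-point target and the 3.30-point source effect, so an observed difference of zero would leave both inside the interval.

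**The case against.** **The mismatch is not demonstrated.** The pooled trials may have used sham, rehabilitation, cognitive training or a mixture as control. This stands. A reader might infer that the source comparator was weaker than this trial's, or that the true sham-controlled effect is below 0.40. The documents show neither; they show only that the claim of caution has no stated basis for this contrast.

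**The Limitations sentence concerns training, not sham.** It ties the possible loss of contrast to cognitive training in both arms, says only that it may occur, and does not mention sham. This also stands. That sham needling matters to the contrast follows from the Sham Acupuncture Procedure and Brand New Insights sections, which define what is compared without giving a size.

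**The lower limit is not a comparator adjustment.** Correct: 2.19 reflects sampling uncertainty in the pooled mean. A reader might take the fall in power from d=0.40 to d=0.29 as the cost of the sham comparator. It is not, and the documents give no figure for that cost. Sizing on a point estimate with a modest discount is also common practice, so d=0.29 serves only as a sensitivity value.

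**The SD may be too large for the enrolled patients.** The 7.5 is a general poststroke value, while entry requires a MoCA below 26 and an MMSE above education-specific cutoffs. As an illustration, assume a normal distribution with mean 21.1 and SD 7.5, truncated to 0–25. The SD is then about 5.1, and 2.19 points gives d of about 0.43. The break-even SD is 2.19 / 0.40 = 5.5. So the statement that the lower limit falls below 0.40 depends on the plan's own SD. That is baseline spread, not a known 8-week SD. It does not affect power at d=0.40, which does not depend on the SD.

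**Baseline adjustment could recover power.** The fMRI Statistical Analysis section mentions regression adjusted for baseline covariates. At d=0.40, 99 × (1 − 0.88²) = 22.3, or 23 per group. A baseline-to-8-week correlation of about 0.88 or more would therefore be needed to approach 22 per group, and the Sample Size section assumes none.

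**Conclusion.** The point holds in two parts.

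First, describing d=0.40 as conservative is unsupported for real versus sham needling added to cognitive training. The description rests only on 0.40 being below 0.44 against an unspecified control, with a 9% allowance, while the plan itself says the contrast may be reduced. The true effect may still be 0.40 or larger.

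Second, the stated 80% power is not delivered at the stated effect. For the two-sample t test the plan names, it is 25% (22 per group) to 30% (27 per group) at d=0.40, and 16% to 18% at d=0.29. Most of the shortfall comes from 44 patients not following from d=0.40, so naming the comparator would not by itself repair the calculation.

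The d=0.29 figures assume an SD of 7.5; the d=0.40 figures assume only an unadjusted two-sided 5% test.

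**What to change.** In Sample Size:

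1. Delete the clause calling d=0.40 conservative.
2. State that the target contrast is real versus sham needling added to cognitive training, and say what control the 3.30-point difference came from.
3. Replace the 80% figure with the power of the 54-patient trial at d=0.40, and give d=0.29 as a sensitivity value. If a baseline-adjusted analysis is meant to carry the power, state the assumed correlation.

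In the statistical analysis section, and in the Discussion where it anticipates a significant effect, say that the MoCA comparison will be presented as an estimated difference with a confidence interval, so that a null result is not read as evidence of no effect.

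The cost is rewording and a short recalculation. No added enrolment is asked for and conduct does not change. The Results section reports no participants enrolled as of August 2025, so the correction can precede any data. The downside is a less favourable stated power.

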### Participants and Recruitment

We aim to enroll 54 participants through a combination of ward visits and online promotional efforts. Individuals expressing interest in participating will undergo eligibility assessment conducted through a screener, typically via contact at the recruitment office. A MoCA score of <26 is used as the primary cutoff to identify cognitive impairment in accordance with the standard diagnostic threshold recommended in clinical guidelines and previous studies. Patients scoring below this threshold are considered eligible for inclusion. In cases of low educational level (≤12 years), 1 point is added to the total MoCA score as per standard adjustment procedures. Should the applicant satisfy the research criteria, an invitation to partake in the study will be extended. Figure 1 shows the flow diagram of participants.

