### Eligibility Criteria

Eligible participants must meet the specified inclusion criteria and not fall under the exclusion criteria. The inclusion criteria are as follows: confirmation of the diagnosis through adherence to the stipulated criteria and validation via head magnetic resonance imaging (MRI) or computed tomography examination; disease duration of >1 month; first ever stroke to avoid confounding effects of previous cerebrovascular events on brain network reorganization and cognitive function; conscious state with stable vital signs and nonprogressive symptoms; clear consciousness without meeting the criteria for *dementia* (Mini-Mental State Examination [MMSE] score of >17 for illiterate individuals, >20 for individuals with a primary school educational level, and >24 for individuals with a middle school educational level or higher—thresholds selected to ensure that participants can complete the full range of cognitive assessments while still presenting mild to moderate PSCI); onset of cognitive impairment after stroke; age of >18 years; right-handedness to reduce variability in brain lateralization patterns, which is particularly important for imaging analyses; and voluntary participation with the provision of self- or legal guardian–signed informed consent.

Exclusion criteria encompass recurrent disease; cognitive impairment originating from other causes; the presence of severe conditions such as liver, kidney, or heart disease; and impediments to cooperation with examinations due to severe hearing impairment, language barriers, or other significant reasons. In addition, all potential participants will be assessed using validated screening tools such as the Hospital Anxiety and Depression Scale or Hamilton Depression Rating Scale at baseline. Patients who meet the diagnostic threshold for moderate to severe depression or anxiety (Hospital Anxiety and Depression Scale score of ≥11 or Hamilton Depression Rating Scale score of ≥17) will be excluded from the trial to avoid emotional state confounding cognitive outcome assessments.

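### The SD of 7.5 MoCA points behind d=0.44 is not shown to apply to the patients this trial will enrol and is very probably too large for them

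*Protocol article*

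**What the plan says.** The Sample Size section of the protocol article sets an "effect size of *d*=0.40 on the MoCA at 8 weeks". It supports this with a meta-analysis "showing a pooled mean difference (MD) of 3.30 points (95% CI 2.19-4.40) versus control" and converts the points to a standardized effect: "Using representative poststroke variability (MoCA score mean 21.1, SD 7.5), an MD of 3.30 corresponds to a standardized effect of approximately 0.44". The section concludes "thus *d*=0.40 is conservative". With a two-sided α of 0.05 and power of 0.80 it then gives 22 per group, raised to 27 per group (54 in total) for 20% dropout.

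Entry is narrower than poststroke patients in general. Under Participants and Recruitment, "A MoCA score of <26 is used as the primary cutoff to identify cognitive impairment", and patients below it are eligible. Under Eligibility Criteria, dementia is excluded by an "Mini-Mental State Examination [MMSE] score of >17 for illiterate individuals, >20 for individuals with a primary school educational level", with a floor of above 24 for middle school or higher. That section says the floors are meant to leave mild to moderate impairment.

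**The concern.** An SD used to standardize a target difference should describe the analysed quantity in the patients to be analysed. Here it carries a general poststroke label, while the trial cuts the score range directly at the top and indirectly at the bottom. One SD above the stated mean is 21.1 + 7.5 = 28.6, beyond the entry cap of 25. Restricting the range normally shrinks the SD, so the same 3.30 points becomes a larger d, and the same d=0.40 becomes fewer points.

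Two things are at stake. A reader is told in effect that the trial plans for about 3 points, close to the cited evidence, when d=0.40 probably stands for clearly less. In addition, the sample-size paragraph has to be recalculated for another reason (see the last step of the working), and a recalculation that kept 7.5 would carry the doubtful input forward.

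**Working it through.** **Inputs from the protocol article.** Mean difference 3.30 (95% CI 2.19 to 4.40), mean 21.1, SD 7.5, d=0.40, two-sided α 0.05, power 0.80, 22 per group before dropout (Sample Size); MoCA below 26 (Participants and Recruitment); MMSE floors (Eligibility Criteria); scale maximum 30 (Primary Outcomes).

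**Assumptions, not in the documents.** A normal shape; a range of lower MoCA limits standing in for the MMSE floors; a range for the SD of change.

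1. *The plan's own figure.* d = MD/SD = 3.30/7.5 = 0.44, which reproduces. In points, 0.40 × 7.5 = 3.0. The division is correct; the question is whether 7.5 is the right divisor.

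2. *How much of the source would be ineligible.* Under Normal(21.1, 7.5), about 28% would score 26 or more.

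3. *Baseline SD after the entry cuts.* Normal(21.1, 7.5) on whole scores, restricted to the range shown:

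| MoCA range | SD | 3.30/SD |
|---|---|---|
| 0–25 (upper cut only) | 5.25 | 0.63 |
| 8–25 | 4.54 | 0.73 |
| 10–25 | 4.19 | 0.79 |
| 12–25 | 3.77 | 0.87 |
| 15–25 | 3.05 | 1.08 |

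4. *A check without normality.* Scores between a floor L and 25 with mean m have variance of at most (25 − m)(m − L). If the mean stayed at 21.1, an SD of 7.5 would need 21.1 − L ≥ 56.25/3.9 = 14.4, so L ≤ 6.7, with every patient at one extreme or the other. With L = 10 the maximum SD is √(3.9 × 11.1) = 6.6. For any mean, an SD of 7.5 needs a range of at least 15 points, and at exactly 15 half the patients at each end.

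5. *From baseline to week 8.* The cuts act at entry, and week-8 scores can exceed 25. If change has an SD of 2 to 4 points and is unrelated to baseline, the week-8 SD runs from √(3.1² + 2²) = 3.7 to √(5.3² + 4²) = 6.6. Any tendency of low scorers to gain more would pull this down. A working range of about 3.5 to 6 is reasonable.

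6. *Consequences over that range.* Power is for 3.30 points, two-sample t test, two-sided α 0.05, 22 per group (54 × 0.8 = 43.2, about 22 per group after dropout).

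| SD | d for 3.30 points | Points at d=0.40 | Power |
|---|---|---|---|
| 3.5 | 0.94 | 1.4 | 86% |
| 4.5 | 0.73 | 1.8 | 66% |
| 5.5 | 0.60 | 2.2 | 49% |
| 6.0 | 0.55 | 2.4 | 43% |
| 7.5 (as stated) | 0.44 | 3.0 | 30% |

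7. *The separate sample-size error.* The same test with d=0.40 and 80% power needs about 100 per group (exact solution 99.1). With 22 per group the power at d=0.40 is 25%. For 80% power, 22 per group requires d=0.86, which for 3.30 points means an SD of about 3.30/0.86 = 3.8.

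**The case against.** Several objections have force.

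- *The direction favours the plan.* A smaller SD raises the standardized effect of 3.30 points, so d=0.40 becomes more cautious against that difference. This stands. A reader might infer that the protocol is wrong to call 0.40 conservative; the figures do not support that, since every SD in the range gives d above 0.44.
- *The source may not be unselected.* This stands in part. The article calls the SD representative and does not describe its source population, and the mean of 21.1 lies within the eligible range. That the source includes many ineligible patients is an inference from the label and from 28.6 exceeding the cap.
- *An SD of 7.5 is not impossible under a cap of 25.* Correct. Some distributions over a wide range reach it; scores spread evenly from 0 to 25 are one example. The claim is only that such a spread is hard to square with the MMSE floors and the stated aim of mild to moderate impairment.
- *The model is rough.* Normal(21.1, 7.5) puts about 12% above 30. Restricting it to the legal 0–30 scale, before any entry rule, already gives an SD of 6.2, so part of the fall to 5.25 comes from the scale limits. The MoCA floors are assumed, because the documents set floors only on the MMSE. The truncated SDs are therefore illustrative.
- *The entry cuts act on baseline.* True, and the reason for widening the range. The article calls the outcome a change but sets d on the 8-week score, and gives no eligible-population SD for either.
- *Nothing else depends on 7.5.* The sample size is stated from d=0.40 directly, and the SD serves only the justification. This limits the point's weight but does not remove it, because that justification tells the reader what d=0.40 means.

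**Conclusion.** The point holds as a mismatch between a planning input and the entry criteria, not as an arithmetic error. The SD of 7.5 is not shown to apply to the enrolled patients and is very probably too large. With SDs of about 3.5 to 6, d=0.40 corresponds to 1.4 to 2.4 points instead of 3.0; for SDs below about 5.5 (2.19/0.40) that is less than the lower confidence limit of 2.19 in the cited meta-analysis. These sizes rest on the assumed normal shape, MoCA floors and change SD. The direction is firmer than the exact values.

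A reader might also infer that a smaller SD rescues the sample size. It does not do so in general: with 22 per group, power for 3.30 points reaches 80% only if the SD is about 3.8 or less, and nothing in the documents establishes that. Nor is this mismatch the cause of the low power. The failure of 22 per group to follow from d=0.40 is a separate and larger error.

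**What to change.** In the Sample Size section:

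1. State the target difference in MoCA points.
2. Replace 7.5 with an SD for the quantity to be analysed (week-8 score or change from baseline) in patients meeting this trial's MoCA and MMSE entry rule, give its source, and label it as an assumption.
3. Re-derive the standardized effect from those two figures and rest any statement that 0.40 is conservative on that result.
4. Give the power of the fixed 54 over a range of SDs, as in the second table of the working, in place of the single 80%.
5. Correct in the same revision the derivation of 22 per group from d=0.40.

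The cost is a rewritten paragraph and a short calculation. This point by itself adds no patients. The article reports no enrolment as of August 2025, so the change could be made before data exist. The downside is that the stated power becomes less favourable and openly depends on an assumed SD.

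### The stated minimum of 44 participants does not follow from d=0.40, two-sided 5% and 80% power: the planned t test needs 100 per group, and unadjusted power is about 25% to 30%

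*Protocol article*

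**What the plan says.** All of the inputs are in the Sample Size section of the protocol article. The endpoint is defined there: "The primary outcome of this study is the change in cognitive function as measured using the Beijing version of the Montreal Cognitive Assessment (MoCA"). The assumed between-group effect at 8 weeks is d=0.40. It is supported by a meta-analytic difference of "3.30 points (95% CI 2.19-4.40) versus control" and by a post-stroke SD of 7.5, from which the article derives that "an MD of 3.30 corresponds to a standardized effect of approximately 0.44" and calls 0.40 conservative. The section concludes: "Therefore, the trial is powered on MoCA as the primary cognitive end point".

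With a two-tailed test, alpha of .05 and power of 0.80, the section then reports that "the minimum required sample size was calculated to be 44 participants (22 per group"). For 20% dropout, "the total sample size was increased to 54 participants, with 27 participants allocated to each group".

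The Sample Size section does not name the test that was entered in the software. The section on statistical analysis of general data and efficacy indicators plans two-tailed independent-sample t tests between groups. The fMRI Statistical Analysis section adds multiple linear regression of post-treatment MoCA on group, adjusted for baseline covariates. No correlation between baseline and 8-week MoCA is given anywhere.

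**The concern.** Twenty-two per group is a typical size for detecting a large standardized difference, not one of 0.40. If the inputs are as printed, the stated size is too small by a factor of about 4.5 (100/22), and the 80% attached to the primary endpoint is overstated by more than 50 percentage points.

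This is a false statement about the main design property, and a fuller document could not make 44 follow from the printed inputs. At stake is how the result can be used: a true effect of the planned size would more often than not fail to reach significance in a trial described as having an 80% chance of detecting it. The Results section says that no participants have been enrolled, so the statement can still be corrected before any data exist.

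**Working it through.** **Inputs from the article.** d=0.40 between groups at 8 weeks; two-sided alpha 0.05; power 0.80; mean difference 3.30 (95% CI 2.19 to 4.40); SD 7.5; stated minimum 22 per group; 27 per group enrolled; 20% dropout (all Sample Size). Allocation 1:1 (Randomization and Allocation Concealment). Independent-sample t test (statistical analysis section).

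**1. The effect size reproduces.** 3.30/7.5 = 0.44. At SD 7.5, d=0.40 is 0.40 × 7.5 = 3.0 points.

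**2. The sample size does not.** Normal approximation: n per group = 2 × (1.960 + 0.842)² / d².
- d=0.40: 2 × 7.85 / 0.16 = 98.1, so 99 per group. The exact noncentral t gives 100 (power 80.4%).
- d=0.44: 2 × 7.85 / 0.1936 = 81.1, so 82 per group. The exact t gives 83.
- The article states 22 per group. A one-sided test would still need 78 per group at d=0.40.

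**3. Unadjusted power of the design as sized.** Noncentrality = d × √(n/2); at 22 per group and d=0.40 this is 0.40 × √11 = 1.33, against a critical t of 2.02 on 42 degrees of freedom.

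| Evaluable | Power, d=0.40 | Power, d=0.44 | d for 80% power |
|---|---|---|---|
| 22 + 22 | 25.4% | 29.7% | 0.86 |
| 21 + 22 (54 × 0.8 = 43.2) | 24.9% | 29.1% | 0.88 |
| 27 + 27 | 30.3% | 35.5% | 0.78 |

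A d of 0.86 at SD 7.5 is 6.5 points, above the upper limit of the cited interval (4.40).

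**4. Can baseline adjustment rescue 22 per group?** The correlation r between baseline and 8-week MoCA is not given, so it is assumed here. With ANCOVA the residual SD is √(1 − r²) times the raw SD, and one degree of freedom is lost.

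| Assumed r | Power, 22 per group | Power, 27 per group |
|---|---|---|
| 0.5 | 32% | 38% |
| 0.6 | 37% | 44% |
| 0.7 | 44% | 52% |
| 0.8 | 58% | 67% |

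Reaching 80% needs r of about 0.89 at 22 per group, or 0.86 at 27 per group. An analysis of change scores, with SD √(2(1 − r)) times the raw SD, also needs r of about 0.89 at 22 per group (normal approximation).

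**5. Can another test explain 44?** Two come close, but neither is the stated comparison.
- A paired or one-sample t test at d=0.44 needs 43 in total. It does not compare groups.
- A three-visit group-by-time F test with f=0.20 and an assumed correlation of 0.5 needs 42 and has 82% power at 44. But f=0.20 is not what d=0.40 at 8 weeks implies for that interaction. If the group difference grows as 0, 0.2 and 0.4 SD over the three visits, f = √((0.01 + 0 + 0.01)/3) = 0.08. That needs about 244 in total and has about 20% power at 44.

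**The case against.** The best defence is that 44 was produced by a repeated-measures option in the software, and that the baseline-adjusted regression is more efficient than a plain t test. The Sample Size section does not name the test, so the first part is possible. It does not help, because such a run would not power the 8-week between-group contrast to which the section attaches d=0.40. The second part has some force: 25% belongs to d=0.40, an unadjusted test and about 22 completers per group, and is not a fixed property of the trial. More evaluable participants or baseline adjustment would raise it, but not to 80% over the assumed range of correlations.

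Three stronger readings are tempting and should not be made.

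- **That the SD of 7.5 makes d=0.40 too optimistic.** Entry is restricted: "A MoCA score of <26 is used as the primary cutoff to identify cognitive impairment", and dementia is excluded on the MMSE. But a narrower spread would make a fixed 3.30 points a larger standardized effect, so 0.40 would become more cautious, not less. For example, 3.30 points at an SD of about 3.8 is d=0.86, which 22 per group could detect with 80% power. The article does not state that assumption. It sets no MoCA floor either, and the entry cap does not bind at 8 weeks, so no SD can be derived by truncation. On the article's own figures, 0.40 is below 0.44, and calling it conservative relative to the pooled estimate is fair.
- **That the dropout allowance is a material error.** 44/0.8 = 55, or 28 per group (22/0.8 = 27.5), against the 54 stated; 22 × 1.2 = 26.4, rounded up to 27, would explain it. This is a one-participant difference and at most a minor note.
- **That the investigators will take a null result as proof of no effect.** The article does not say so.

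**Conclusion.** The point holds and must be corrected. The minimum of 44 does not follow from the article's own inputs; the planned unadjusted comparison needs 200 evaluable participants at d=0.40, or 166 at d=0.44. With the enrolment planned, unadjusted power at d=0.40 is about 25% (around 43 or 44 completers) to 30% (all 54 evaluable), and 80% power is reached only for d of about 0.78 to 0.88.

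These figures take d=0.40, 1:1 allocation and the two-sided 5% t test as stated. The adjusted figures, about 32% to 58% at 22 per group and 38% to 67% at 27, rest on assumed correlations of 0.5 to 0.8. The finding is that the stated power is wrong. It does not show that the assumed effect is overoptimistic, nor that the trial has to enrol 200 participants.

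**What to change.** Keep 54 participants and rewrite the Sample Size paragraph. Remove 44 (22 per group) as the requirement for d=0.40, and remove the statement that the trial is powered on the MoCA. Then do one of the following.

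1. State what 54 enrolled participants deliver: about 25% to 30% power for d=0.40 with the unadjusted t test, and 80% power only for d of about 0.78 (all evaluable) to 0.88 (about 43 completers).
2. Rebuild the calculation in MoCA points. Give the target difference, an SD justified for the eligible population, and the baseline-to-8-week correlation used in a baseline-adjusted primary analysis, with a source for each. Name the test, and report the power that results, whatever it is.

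The dropout line can be tidied in the same edit, either as 28 per group or as about 43 expected completers from 54.

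The cost is one paragraph and a less favourable stated power under option 1. No additional participants are needed for the correction. As this changes the stated statistical basis of the trial, the revised text should follow the amendment route set out under Ethical Considerations.
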